**Figure 1 F1:**
[figure not shown]
**Sample size and segmentation into strata of different antidiabetic-treatments.***Legend:* Patients are eligible for inclusion if treated with oral mono or dual combination therapy and are distributed into the following groups: Incretin-based treatments include DPP-4 inhibitors and GLP-1 analogues. Non-incretin-based therapies include metformin, sulfonylureas, acarbose, insulin, alpha-glucosidase inhibitors, and SGLT2-inhibitors.

### Recruitment plan

Patient enrolment has started in July 2012. It is estimated that the first visit of the last patient enrolled will take place in early 2013, the last visit of the last patient is planned for early 2015. The Clinical Study Report will then be published in April of the following year. Figure 
2 gives an overview of the timelines and the points when interim analyses to be performed.

**Figure 2 F2:**
[figure not shown]
**Estimated enrolment and planned interim-analyses as well as follow-up periods.***Legend:* IA, Interim Analysis, PO, Primary Objective; FU, Follow-up.

### Documented variables

Table 
1 gives an overview of the variables to be documented. Source documentation and data accuracy will be verified by site visits in randomly selected 2% of the sites.

**Table 1 T1:** Overview of documented parameters

**Visit**	**Baseline**	**FU 6 mo**	**FU 12 mo**	**FU 24 mo**
Sociodemographics ^1^	x			
Physical examination ^2^	x			
Cardiovascular concomitant diseases ^3^	x	x	x	x
Diabetes associated diseases ^4^	x	x	x	x
Available laboratory values^5^	x	x	x	x
Antidiabetic medication^6^	x	x	x	x
Additional current medication	x	x	x	x
Hypoglycaemic events^8^	x	x	x	x
QoL (EuroQoL-5D)	x	x	x	x
Patient reported outcomes (PRO)	x	x	x	x

*Legend:* 1) age, gender, insurance status, DMP participation, education, employment status, care level 2) weight, height, waist circumference, smoking, alcohol consumption, physical activity 3) coronary heart disease, previous myocardial infarction, previous PCI, previous CABG, previous stroke, heart failure (NYHA) peripheral artery occlusive disease 4) dyslipidemia, amputation, autonomous neuropathy, non- proliferative/proliferative retinopathy, diabetic macular edema, blindness, dialysis other 5) less than six weeks old: lipid values (fasting total cholesterol, fasting LDL, fasting HDL, triglycerides), fasting and post-prandial blood glucose, HbA1c, renal values (serum creatinine, microalbustix albumin, microalbustix creatinine), liver parameters. 6) metformin, sufonylureas, glucosidase inhibitors, glinides, glitazones, DPP-4 inhibitors) 7) ACE inhibitors, ARBs, renin inhibitors, beta blockers, calcium channel blockers, diuretics, other) 8) 12 months before baseline visit and since baseline or last FU, respectively.

### Quality assurance

There are three strategies for data quality checks: validations that occur at the time of data entry (i.e., “front-end”), a second, more sophisticated quality control program that runs as a prelude to the creation of the analysis data set and on-site data monitoring.

Front-end data checks are advantageous because mistakes are caught and corrected at the time of entry – a system that is efficient for data collectors. Certain data elements can be required, while other variables may allow for missing values. Additionally, parameters will be defined to allow entry of only those records that meet inclusion criteria.

Prior to the creation of the analytic dataset, more extensive quality control processes are performed. These checks, programmed in SAS, include parent–child edits, consistency edits, and data transformations that will facilitate analyses.

Source documentation and data accuracy will be verified by site visits in randomly selected 2% of the sites.

### Statistical methods

All variables collected in the eCRF as well as the data obtained from the quality of life assessments and all derived parameters will be used in the statistical analysis. Binary, categorical, and ordinal parameters will be summarised by means of absolute and percentage numbers within the various categories (including ‘missing data’ as valid category at baseline). Numerical data will be summarised by means of standard statistics (i.e. number of available data, number of missing data, mean, standard deviation, minimum, median, maximum, lower and upper quartile). In addition, adequate graphs (e.g. bar charts, box-whisker plots) may be presented to summarise the results for some parameters. Time-to-event variables will be analysed via a Cox proportional hazard regression model presenting hazard ratios and the corresponding 95% confidence intervals. In addition Kaplan-Meier curves will be presented for these variables. Two-sided 95%-CI will be presented for important parameters, but should be interpreted in an exploratory descriptive way. Further multivariable analyses will be performed according to the statistical analysis plan (SAP). Formal statistical tests will not be performed within the statistical analysis. A report including descriptive statistics of all documented parameters will be generated for the overall patient population. Depending on the variable(s) of interest, additional selection criteria for patients (e.g. subgroup analyses) considered in specific analyses may be used, if considered useful during the statistical analysis. Details on the selection criteria used will be given in the SAP and in the statistical section of the report. The statistical analysis will be performed using SAS (release 9.2 or higher; Cary, NC, USA).

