**Methods:**

DIALOGUE is a prospective observational German multicentre registry and will enrol 10,000 patients with both diabetes and hypertension in up to 700 sites. After a baseline visit, further documentations are scheduled at 6, 12 and 24 months. There are two co-primary objectives referring to the most recent guidelines for the treatment of diabetes and hypertension: 1) individual HbA1c goal achievement with respect to anti-diabetic pharmacotherapy and 2) individual blood pressure goal achievement with different antihypertensive treatments. Among the secondary objectives the rate of major cardio-vascular and cerebro-vascular events (MACCE) and the rate of hospitalizations are the most important.

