### Secondary objective

Secondary objectives are (1) to document major cardio-vascular and cerebro-vascular events (MACCE) during 2 year follow-up; (2) to document hospitalizations during 2 year follow-up; (3) to assess the proportion of patients reaching blood glucose target values without experiencing the following adverse effects: peripheral oedema or proven hypoglycaemic events or discontinuation due to gastrointestinal events or significant weight gain (>5 %); (4) to describe patient characteristics in patients with diabetes mellitus and hypertension in clinical practice in the overall registry population; (5) to document anti-diabetic and anti-hypertensive therapy and its impact on treatment target achievements in diverse subject populations, which have to be pre-specified by the scientific committee (e.g. females versus males, age </>75y, patients on insulin versus patients not on insulin, etc.); (6) to verify the applicability of and the adherence to the current guidelines for the treatment of diabetes and hypertension in clinical practice; (7) to document utilisation patterns of drugs used for the treatment of diabetes as well as hypertension in clinical practice; (8) To evaluate adverse cardio-vascular events as well as diabetes-related micro-vascular and macro-vascular events; (9) to evaluate the glycaemic profiles of the participants with regards to differences in anti-diabetic treatment patterns; (10) to evaluate the blood pressure profiles; (11) To evaluate co-morbid disease conditions; (12) to evaluate the change in BMI over the course of the study; (13) to evaluate the proportion of patients with hypoglycaemic events over the course of the follow-up; (14) to evaluate cardio-vascular risk by using validated cardio-vascular risk scores such as the EURO Score; (15) to evaluate health status (EQ-5D); (16) to determine costs associated with the treatment and disease related complications; (17) to document treatment persistence over time, change in treatments / dosing during a follow-up of two years (optional up to 4 years of follow-up); (18) to document patient reported outcome (PRO).

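### Kaplan-Meier curves are set for every time-to-event variable; where death precludes the event and is censored, one minus the curve overstates the proportion of patients affected

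*Protocol article*

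**What the plan says.** The Statistical methods section of the protocol article fixes both the model and the display for time-to-event data. The model is given as "Time-to-event variables will be analysed via a Cox proportional hazard regression model presenting hazard ratios and the corresponding 95% confidence intervals". The display follows directly: "In addition Kaplan-Meier curves will be presented for these variables". No exception is named, and the article does not mention competing events, cumulative incidence functions or the handling of death.

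The same section defers two things to the SAP: further multivariable analyses, and the criteria for selecting patients into specific analyses. It does not defer the choice of curve. Confidence intervals are to be read as exploratory, and no formal tests are planned.

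The article never says which variables are time-to-event. The Secondary objective section offers three candidates: "to document major cardio-vascular and cerebro-vascular events (MACCE) during 2 year follow-up", "to document hospitalizations during 2 year follow-up" and "to document treatment persistence over time". The components of MACCE are not given. The Methods part of the abstract singles out the MACCE rate and, in its words, "the rate of hospitalizations are the most important" among the secondary objectives.

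**The concern.** Kaplan-Meier treats a censored patient as someone whose later risk equals that of patients still under observation. That is reasonable for a patient lost to follow-up for unrelated reasons. It is not reasonable for a patient who has died, who can no longer be hospitalised or stop a drug. With deaths censored, one minus Kaplan-Meier estimates risk in a hypothetical population in which nobody dies. Whenever deaths occur it lies above the proportion of real patients who have the event.

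The point matters more in a descriptive registry than in a trial built around a hazard ratio. With no formal tests, the absolute level is much of the result, and the stated purpose is to describe outcomes in daily practice. The excess also grows with mortality, so curves for strata with different mortality would be raised by different amounts.

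**Working it through.** The article states no event rate, mortality or precision target, so there is no figure of its own to reproduce. The check shows the direction of the bias and its size over an assumed range.

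**Inputs from the article:** 10,000 patients and 24 months of follow-up (Methods/Design); two-sided 95% intervals (Statistical methods).

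**Assumed, not in the article:** two-year event risk H, as read from one minus Kaplan-Meier with deaths censored; two-year mortality D; constant, independent hazards.

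**Formulas,** with T = 2 years:
- event hazard h = −ln(1 − H)/T; death hazard m = −ln(1 − D)/T
- true cumulative incidence CIF = h/(h + m) × [1 − exp(−(h + m)T)]
- excess = H − CIF
- half-width = 1.96 × √(H(1 − H)/n)

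**One case in full,** H = 30%, D = 4%:
- hT = −ln(0.70) = 0.3567 and mT = −ln(0.96) = 0.0408
- h/(h + m) = 0.3567/0.3975 = 0.8973
- 1 − exp(−0.3975) = 1 − 0.70 × 0.96 = 0.3280
- CIF = 0.8973 × 0.3280 = 0.2943, so the excess is 0.57 points

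A simulation of 2,000,000 patients with these hazards gave 30.0% for one minus Kaplan-Meier and 29.4% for the actual proportion with the event.

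**Range at two years, H = 30%:**

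| Two-year mortality | CIF | Excess (points) |
|---|---|---|
| 2% | 29.72% | 0.28 |
| 4% | 29.43% | 0.57 |
| 6% | 29.14% | 0.86 |
| 10% | 28.56% | 1.44 |
| 15% | 27.82% | 2.18 |

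The half-width is 1.96 × √(0.30 × 0.70/10,000) = 0.90 points at n = 10,000 and 2.01 points at n = 2,000. For the whole cohort, the excess stays within the half-width up to 6% mortality and passes it at 10%.

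**Other event risks:** at H = 10% the excess is 0.10 points at 2% mortality, 0.20 at 4% and 0.50 at 10%. At H = 50% it is 0.44, 0.89 and 2.26 points. In relative terms the overstatement is roughly half the two-year mortality: about 1% at 2%, 2% at 4% and 5% at 10%.

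**A higher-mortality stratum** (illustrative; no source in the article): with H = 40% and D = 10% the CIF is 38.13% and the excess 1.87 points. The half-width at n = 2,000 is 2.15 points.

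**Longer follow-up:** secondary objective 17 allows an optional extension to four years. Running the same hazards on, one minus Kaplan-Meier is 1 − 0.70² = 51%.
- D = 4% at two years: CIF = 0.8973 × (1 − 0.49 × 0.9216) = 49.2%, an excess of 1.8 points.
- D = 6% at two years: CIF = 0.8522 × (1 − 0.49 × 0.8836) = 48.3%, an excess of 2.7 points.

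The half-width at n = 10,000 is then 1.96 × √(0.51 × 0.49/10,000) = 0.98 points.

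**The case against.** The strongest reply is that this belongs in the SAP. A condensed article may name Cox and Kaplan-Meier in general terms and leave endpoint definitions, censoring and competing events to a document not shown here. That carries weight for the definitions, and their absence is not the complaint. It carries less for the estimator, because the article chooses one, applies it to all time-to-event variables and does not list it among the matters deferred.

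Several stronger readings are tempting, and the article does not support them.
- **Hospitalisation and persistence will be analysed by Kaplan-Meier.** The article does not classify either as time-to-event. Hospitalisation is to be documented and is called a rate in the abstract. It could be reported as a count and percentage under the rule for binary data, which would not carry this bias.
- **The registry's reported event rates are overstated.** The article promises curves alongside hazard ratios. It does not say that one minus Kaplan-Meier will be the reported rate, and it states no censoring rule. MACCE may include all deaths, in which case the problem does not arise for it.
- **Comparisons of older and younger patients will be distorted.** The split "females versus males, age </>75y" appears in objective 5, which concerns reaching treatment targets, and only as an example still to be settled by the scientific committee. No time-to-event comparison by age is described.
- **Patients who die stay in the risk set.** They do not; censoring removes them. The error is that they are implicitly given the later hazard of survivors.

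Two further objections stand. Eligibility is limited to patients on oral mono- or dual therapy and excludes known cancer, so low mortality is a realistic part of the range, and there the excess is small. A Cox model with death censored estimates a valid cause-specific hazard ratio; it needs a label, not replacement.

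**Conclusion.** The point holds conditionally. Kaplan-Meier is prescribed without exception. For any time-to-event variable that death precludes, one minus the curve will exceed the true proportion affected if deaths are censored and the curve is read as incidence. The direction is certain once any deaths occur before the event; the size is not, because it rests wholly on assumed mortality, event risk and constant independent hazards. At a 30% two-year event risk it runs from about 0.3 points at 2% mortality to 1.4 at 10%, against a half-width of 0.9 points in the full cohort. At a 10% event risk and 2% mortality it is only 0.1 points. It is larger in strata with higher mortality and with follow-up beyond two years. Only secondary, descriptive objectives are affected, so this is a minor improvement; neither co-primary objective depends on it.

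**What to change.** Amend the Kaplan-Meier sentence under Statistical methods along these lines:
- Time-to-event variables that death precludes are shown as Aalen-Johansen cumulative incidence curves, with death as a competing event.
- Kaplan-Meier is kept for all-cause death and for composites that include all-cause death.
- Cox hazard ratios for the precluded variables are described as cause-specific.

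The cost is a sentence or two of text, a procedure option or macro in the SAS analysis already planned, and one more type of curve to explain to readers. It also requires dates of death; the article does not say whether these are recorded, so that should be confirmed.

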## Discussion

There are a number of epidemiological studies, which documented (among other aspects) the treatment of type-2 diabetes in Germany. Table 
2 gives an overview of those studies closely related to the objectives of DIALOGUE. These include DUTY 
[34], DIG 
[35-37] and DiaRegis 
[2,38-40]. DUTY (2001–2003) was among the first 
[34] to prospectively document the effect of a tailored intervention on blood glucose and CV risk factor target achievement. They demonstrated that too many patients suffering from diabetes mellitus do not receive consistent therapy for cardiovascular risk factors according to guidelines and therefore the required target values were rarely reached. DIG 
[35-37] started one year later (2002) and had a four year follow-up and meant to document guideline-oriented treatment across Germany. A major secondary focus was to investigate the metabolic syndrome in Germany. DiaRegis 
[2,38-40] is a prospective registry focussing on the role of hypoglycaemia on subsequent vascular events. Throughout the follow-up a steady increase in the incidence of vascular events was documented, suggesting an association between hyperglycaemia and vascular events 
[41].

**Table 2 T2:** Comparison of DIALOGUE with other existing registries

	**DIALOGUE**	**DiaRegis**	**DIG**	**DUTY**
Reference		[2,38-40]	[35-37]	[34]
No. of physicians	Up to 700	313	238	n.a.
No. of patients	Up to 10,000	3,810	4,020	59,035
Recruitment	Starting 06/2012	06/2009–03/2010	2002-2004	2001-2003
Follow-up	2-4 years	2 years	4 years	9 months
Design	Prospective cohort	Prospective cohort	Prospective cohort study	Prospective cohort study
Monitoring for data verification	Yes (2%)	Yes (10%)	None	None
Proportion T2D	100%	100%	100%	100%
Patients	Co-morbid disease of diabetes and hypertension	Patients on oral mono- or dual antidiabetic combination therapy	Type-2 Diabetes mellitus	Type-1 or type-2 diabetes mellitus
Median age (years)	n.a.	65.9	Mean 61.8 ± 8.1	64.4 ± 11.7
Female (%)	n.a.	46.7	46.8	50.9
BMI (median)	n.a.	30.0	Mean 30.7 ± 5.2	Mean 28.7 ± 4.8
Focus	Target achievement with respect to HbA1c and blood pressure	Hypoglycaemia incidence with antidiabetic drug use	Application of guidelines in clinical practice	Effect of tailored intervention on target achievement

*Legend.* n.a., not available.

Most of these studies however either had a detailed look on the prevalence of type-2 diabetes in primary care practice (HYDRA and DETECT), the co-morbidity burden (DETECT), the costs (CODE-2, CoDiM and ROSSO), or on self-monitoring of blood glucose (ROSSO). Some were also retrospective in design (CODE-2, CoDiM and ROSSO). Similar to DIALOGUE the effect of a tailored intervention on target achievement was investigated in DUTY and DIG. The added value of DIALOGUE is, that it will enrol almost 10,000 patients exclusively with the co-morbid disease constellation diabetes *and* hypertension and the effect of two matching treatment approaches on target goal achievement as to the more recent guidelines which suggest more individualized treatment targets 
[33,42,43] based on increasing calls for a move toward more patient-centred care 
[44,45].

## Conclusions

DIALOGUE is the first registry that focuses at the evaluation of T2D patients who also suffer from hypertension, addressing both achievement of glycaemic and anti-hypertensive goals considering the individualized treatment targets as recommended by recent guidelines. As the combination of both diseases is a major factor in the development of vascular complications, data obtained will help to explain the gap between the inadequate glycaemic and blood pressure control in the “real world setting” despite the demonstrated efficacy and safety of anti-diabetic and anti-hypertensive drugs in clinical trials.

## Abbreviations

MACCE: Major Cardiovascular and Cerebrovascular Events; MAGE: Mean Amplitude of Glycaemic Excursions; T2D: Type-2 Diabetes Mellitus; UKPDS: United Kingdom Prospective Diabetes Study; ACEI: ACE-inhibitor; ARB: Antiotensin Receptor Blocker; RAAS: Renin Angiotensin Aldosterone System.
